### Key objectives

To determine the yield of screening for previously unrecognized HF, COPD and other chronic diseases (like anaemia, renal dysfunction, thyroid disorders) in frail elderly with reduced exercise tolerance and/or exercise induced dyspnoea.

To assess the effect of the diagnostic screening and subsequent targeted interventions on functional health and health related quality of life after 6 months of follow-up.

To assess the cost-effectiveness of screening and subsequent targeted management.

To identify the most cost-effective combination of screening tests.

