### Outcome measures

#### HF and COPD

The presence of HF and/or COPD present or absent will be determined six months after the initial investigations by an outcome panel that will evaluate all diagnostic test results and the effect of treatment during six months follow-up.

For the diagnosis of COPD, airflow obstruction with spirometry is a prerequisite and defined as a post-dilatory ratio of the forced expiratory volume in one second (FEV1) to the forced vital capacity (FVC) <0.70 (FEV1/FVC ratio <0.70). To classify the severity of obstruction, the GOLD-criteria [11] will be applied by the panel.

For the diagnosis of HF, the panel applies the criteria of the European Society for Cardiology (ESC) [4]. HF is considered present when participants have suggestive symptoms (i.e. breathlessness at rest or on exercise, fatigue, tiredness, ankle swelling) and signs (i.e. pulmonary rales, raised jugular venous pressure, peripheral oedema, laterally displaced apical beat) in combination with objective echocardiographic evidence of cardiac dysfunction at rest. In participants who use diuretics for hypertension, signs of volume overload could be masked and therefore in these participants signs of fluid overload are not obligatory. Participants classified as HF by the panel will further be classified as systolic HF, heart failure with preserved ejection fraction (HFPEF) or right-sided HF (cor pulmonale).

For systolic HF, participants need to have a left ventricular ejection fraction (LVEF) ≤45%. To diagnose HFPEF, there must be echocardiographic evidence of diastolic structural or functional abnormalities (abnormal left ventricular relaxation or diastolic stiffness), left atrial enlargement or left ventricular hypertrophy (LVH) in combination with a LVEF >45% [18]. Participants with echocardiographically-determined LVH and an indexed left atrial volume of ≥34 ml/m^2^ or tissue Doppler abnormal mitral inflow or pulmonary venous flow profile are also classified as having diastolic dysfunction. In participants with atrial fibrillation (AF) a complete diastolic assessment is not feasible and therefore we consider an elevated indexed LA volume sufficient to classify diastolic dysfunction in participants with AF. Isolated right-sided HF is defined as increased pulmonary artery pressure (calculated systolic pulmonary artery pressure >40 mmHg) and a LVEF >45%.

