### Final diagnosis by the panel

The final diagnoses are set by a joint panel consisting of three members, a cardiologist, a pulmonologist and a GP. Consensus diagnosis by the panel will be our reference test for the diagnosis of COPD and HF, in case of any discongruence with the classification described before. This is an established method in case an irreproachable reference standard is lacking, as is the case for HF [22]. In case of no consensus the majority decision will be used. In analogy with earlier studies, the panel will use all available information from the diagnostic and follow-up results: the latter to include the effect of targeted therapy in the decision whether a disease is present. The reproducibility of the panel diagnoses will be evaluated by re-testing a random sample of 10% by the same outcome panel.

The joint panel evaluation is divided in three steps; step 1 history taking, physical examination, blood tests, ECG and spirometry, step 2 adding NT-pro-BNP and step 3 adding echocardiography and follow-up. After step 1 and 2 the panel gives a percentage (0-100%) of their suspicion for the different outcomes. With this, we can evaluate how the panel reaches their final diagnoses (set at step 3) and which investigations add most in reaching this decision.

The above evaluation is also done individually by a GP, a pulmonologist and a cardiologist, but the procedure is changed slightly by dividing step 3 in two steps whereby step 3 includes only echocardiography and at step 4 the follow-up is included and the final diagnoses are made. We will evaluate this individual approach and compare it with the more time consuming joint panel evaluation.

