### Statistical analyses

The yield of previously unrecognized HF and COPD (and other diseases) will be calculated as a proportion with 95% confidence intervals in both arms of the trial. The absolute difference in yield between the arms will then be calculated together with its 95% confidence interval. We will also calculate how many participants in the diagnostic screening group were initially incorrectly diagnosed with COPD or HF.

The difference in functional health and quality of life between the diagnostic screening and care as usual groups at 6 months will be compared taking into account potential baseline difference of relevant parameters at baseline (ANCOVA), although such differences are expected to be minimal because of the randomization procedure.

Multivariable regression analysis with receiver operating characteristic (ROC) curves and percentages correctly diagnosed participants will be used to analyze which of the test used in the diagnostic screening are most predictive or necessary for setting the diagnosis of HF and COPD in the study group. A multilevel approach is used in the analyses to correct for the fact that we randomized at the GP practice and not at the patient level.

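### The analysis ranking the screening tests scores them against a panel diagnosis that uses those tests, and the joint panel's ratings cannot separate echocardiography from follow-up

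*Protocol article*

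**What the plan says.** The Statistical analyses section of the protocol article will use multivariable regression, ROC curves and percentages correctly diagnosed to "analyze which of the test used in the diagnostic screening are most predictive or necessary for setting the diagnosis of HF and COPD". One of the key objectives is "To identify the most cost-effective combination of screening tests".

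The reference for these analyses is given under Final diagnosis by the panel: "Consensus diagnosis by the panel will be our reference test for the diagnosis of COPD and HF". On what the panel sees, the same section says that "the panel will use all available information from the diagnostic and follow-up results". The criteria are under Outcome measures, HF and COPD. For COPD: "For the diagnosis of COPD, airflow obstruction with spirometry is a prerequisite". For HF, symptoms and signs must be present "in combination with objective echocardiographic evidence of cardiac dysfunction at rest"; signs of fluid overload are waived for participants taking diuretics for hypertension.

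The joint panel works in three steps. Step 1 covers history, examination, blood tests, ECG and spirometry, followed by "step 2 adding NT-pro-BNP and step 3 adding echocardiography and follow-up". A suspicion of 0 to 100% is recorded after steps 1 and 2, and the final diagnosis is made at step 3. The stated use is to learn how the panel arrives at its diagnosis and "which investigations add most in reaching this decision". A GP, a pulmonologist and a cardiologist also assess individually, with echocardiography alone at step 3 and follow-up at step 4. The article plans to compare the two approaches.

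**The concern.** A test that helps to make the reference diagnosis agrees with that diagnosis partly because it was used to make it. The agreement then overstates what the test says about disease, most of all where the written criteria make the test a condition of the diagnosis. Asking whether spirometry is necessary for COPD, or echocardiography for HF, has its answer largely fixed before any patient is seen. The other tests are then ranked beside two whose place is assured.

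The joint panel's ratings have a different weakness. They are meant to show what each investigation contributes, but echocardiography arrives together with six months of follow-up.

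What is at stake is the choice of tests for a leaner screening programme. If the ranking reflects how the reference was built, it is a poor guide to which tests to keep.

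**Working it through.** The plan states no figure on this point, so there is nothing to reproduce. The check sets the sections side by side and adds an illustration.

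**1. COPD.** The written criteria require a post-dilatory FEV1/FVC below 0.70. So P(ratio < 0.70 | COPD) = 1 by definition, except where panel consensus departs from the criteria.

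**2. HF.** In the same way, P(echocardiographic dysfunction | HF) = 1 under the written criteria. Echocardiography is necessary here but not sufficient, since symptoms and usually signs are also needed. For a yes/no test, AUC = (sensitivity + specificity) / 2. If 40% of those without HF had qualifying abnormalities (assumed), AUC = (1 + 0.60) / 2 = 0.80. If 20% had them (assumed), AUC = (1 + 0.80) / 2 = 0.90. The sensitivity is built in; the AUC is not.

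**3. NT-pro-BNP.** It is not among the written HF criteria, but the panel sees it at step 2, before deciding at step 3. It enters the reference through judgement, with a weight that the article does not give.

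**4. Follow-up.** In the screening arm the GP receives all results, preliminary diagnoses and treatment advice (Screening strategy and care as usual). The treatment response later shown to the panel follows from the same tests, so it is not an independent check.

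**5. Illustration of size.** Every input is an assumption: 15% prevalence; mean shifts in diseased against non-diseased of 0.8 SD for the step 1 tests combined, 1.0 for NT-pro-BNP, 1.2 for echocardiography and 0.8 for follow-up; 300,000 simulated patients. Nested logistic models were scored first against true disease, then against a reference made of the top 15% on a weighted sum of the same tests plus follow-up.

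| Scored against | Step 1 | + NT-pro-BNP | + echo | NT-pro-BNP gain | Echo gain |
|---|---|---|---|---|---|
| True disease | 0.715 | 0.819 | 0.894 | 0.104 | 0.075 |
| Panel, neutral weights | 0.764 | 0.891 | 0.979 | 0.127 | 0.088 |
| Panel, echo weighted double | 0.718 | 0.824 | 0.990 | 0.106 | 0.166 |
| Panel, echo weighted triple | 0.687 | 0.778 | 0.994 | 0.091 | 0.216 |

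The apparent echocardiography gain is 0.088 / 0.075 = 1.2 to 0.216 / 0.075 = 2.9 times the true gain. The NT-pro-BNP gain falls on either side of its true value. With double or triple weight, echocardiography overtakes NT-pro-BNP, the reverse of the true order.

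**6. Joint panel.** Ratings exist after step 1 and after step 2. Their difference isolates NT-pro-BNP. The change from step 2 to the final diagnosis contains echocardiography and follow-up together, with no rating in between. The individual readers have that rating, so the two approaches differ in staging as well as in being joint or individual.

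**The case against.** Several objections have force.

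- **The aim may be narrower.** The panel section speaks of how the panel reaches its decision, and describing that is legitimate even though the panel sees the tests. It also defends panels as accepted where no faultless reference exists. This stands for the panel ratings. It does not cover reading the regression as diagnostic accuracy or as grounds for choosing tests.
- **Candidate predictors are not listed by outcome.** True. That spirometry enters the COPD model and echocardiography the HF model is an inference. It is the natural one, since the analysis is of the tests used in the screening and both are among them.
- **The link to the cost-effective combination is inferred.** Also true. The Cost-effectiveness analysis section compares the strategy with usual care. However, the regression is the only analysis described across both sections that ranks individual tests.

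A reader might also infer more than the documents support:

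- *That added value cannot be read at all.* NT-pro-BNP is added alone, the individual readers separate echocardiography from follow-up, and the regression can enter each test separately. The estimates are biased, not unobtainable.
- *That any model with a defining test must reach an AUC near 1.* Item 2 of the working shows otherwise for HF.
- *That NT-pro-BNP must look better than it is.* The direction is not fixed.
- *That there are too few cases.* The sum 0.15 × 395 = 59 counts new HF and/or COPD combined, which is the event count of neither model. The screening arm also has 22 participants with recorded HF and 68 with recorded COPD, whom the panel may confirm or reclassify.

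**Conclusion.** The concern holds in this form. The test-ranking analysis is subject to incorporation bias. For spirometry in COPD and echocardiography in HF, apparent necessity is largely built in by the written criteria. For the other tests, including NT-pro-BNP, bias is possible in either direction. Separately, the joint panel's ratings cannot show what echocardiography adds to its decision, and the joint-versus-individual comparison mixes format with staging.

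The size cannot be derived from the article. The factor of 1.2 to 2.9 illustrates what can happen under assumed inputs; it is not an estimate for this trial. The conclusion itself rests on the text alone, plus the inference that the defining tests are candidate predictors. The effect is confined to the test-value results and to any choice of test combination drawn from them. The comparisons of yield, functional health and quality of life are unaffected by this point.

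**What to change.** 1. **Joint panel.** Record the 0 to 100% suspicion after echocardiography and before follow-up is revealed, as the individual readers do. The cost is one more rating per patient and slightly longer sessions. It has to be taken at the meeting, because it cannot be recovered afterwards.
2. **Regression and ROC analysis.** Treat spirometry for COPD and echocardiography for HF as part of the reference. Make the ROC and correct-classification results for the remaining tests the main test-value analysis. Describe any model that includes a defining test as showing how the panel decides, not as diagnostic accuracy. The cost is a change of wording and no accuracy claim for the two defining tests, whose place in a test combination must then be argued on other grounds. The remaining tests are still seen by the panel, so some incorporation stays and should be stated.
3. **NT-pro-BNP.** As a sensitivity analysis, repeat the HF analysis with HF set by the written criteria, which do not use NT-pro-BNP, in place of panel consensus. State that symptoms and signs remain partly incorporated, since those criteria require them. The components of those criteria are already collected in the screening arm.

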### Cost-effectiveness analysis

The cost-effectiveness of the diagnostic strategy for detection and treatment of (previously unrecognized) HF and COPD (diagnostic screening group) is evaluated and compared with care as usual. Cost-effectiveness is expressed in terms of cost per case of COPD and per case of HF detected, and in terms of cost per Quality Adjusted Life Years gained (Cost-utility analysis). For measuring direct cost, resource quantities are collected prospectively through the electronic medical files from the GPs. Prices are based on market prices or tariffs for the investigations performed under study. Relevant indirect medical costs are taken into account such as participant time invested and travel costs. As the population under study is older than 65 years of age, productivity losses will not be studied. Sensitivity analysis and multivariate uncertainty analysis are performed, conform current Dutch standards for pharmaco-economic research [23].

### Regulation statement

This study is conducted according to the principles of the current version of the declaration of Helsinki and in accordance with the Dutch law on Medical Research Involving Human Subjects Act (WMO).

### Ethics committee approval

The study was approved by the medical ethical committee (METC) of the University Medical Center Utrecht (UMCU), the Netherlands.

## Results of inclusion

Eighteen general practices are included in the study, 8 were randomized to the diagnostic screening intervention and 10 to the care as usual group.

Of the 11.839 patients aged 65 years or older (16% of all registered citizens) enlist with these practices, 35% met the criteria of frailty. The mean age of the 4142 selected frail patients is 75.6 (SD ±6.9) years and 47% is male. In Table 1 patient characteristics, median number of co-morbidities and medication is given for all selected patients. Of the invited frail patients, 73% responded to our invitation and 30% (1249) was willing to participate. Of those frail patients willing to participate, 33% had no complaints of reduced exercise tolerance or dyspnoea (MRC < 2) and therefore are excluded from the study. Patients excluded because they had no complaints were younger (*p* = 0.04) and more often male (*p* = <0.001) as compared to included patients. Eligible patients who refused to participate (*n* = 3301) were slightly older (*p* = <0.001), but they were comparable on gender (*p* = 0.09) compared to participants.

**Table 1 T1:** Characteristics of all invited frail patients (responders and non-responders)

	**All frail patients**^**#**^	**Patients willing to participate**		**Not willing**^**^**^	**No response**^**>**^
		(*n* = 1249)			
		**Dyspnoea**^*****^	**No dyspnoea**^**<**^		
	(*n* = 4142)				
		(*n* = 841)	(*n* = 408)	(*n* = 1774)	(*n* = 1119)
Age (years), mean (sd)	75.6 ± 6.9	74.6 ± 6.3^·^	73.8 ± 6.1^*‡*^	76.3 ± 7.0^*‡*^	75.9 ± 7.2^*‡*^
Male sex, *n* (%)	1956 (47.2%)	419 (49.8%)^†^	270 (66.2%)^*‡*^	763 (43.0%)^*‡*^	504 (45.0%)^*‡*^
Co-morbidities (number), median (IQR)	3 (3–4)	3 (3–4)	3 (3–4)	3 (3–4)	3 (3–4)
Drugs (number), median (IQR)	5 (4–7)	6 (4–7)	5 (3–6)	5 (4–7)	6 (4–7)

^#^All selected frail patients aged 65 years or over, ^*^patients who were willing to participate and fully met the inclusion criteria (MRC dyspnoea ≥2 and/or a positive answer on questionnaire about reduce exercise tolerance), ^<^patients who were willing to participate, but were excluded based on complaints (MRC dyspnoea score ≤1 and only negative answers on the questionnaire about reduce exercise tolerance), ^^^patients who were not willing to participate, ^>^patients who gave no response after sending 2 written invitations. ^*‡*^*P* = <0.05 compared to the patients with dyspnoea, ^†^*p* = ns dyspnoea patients compared to patients not participating in the study (no dyspnoea, not willing and no response), ^·^*p* = <0.05 dyspnoea compared to patients not participating in the study.

Finally, 841 frail patients with complaints of dyspnoea or reduced exercise tolerance were included in the study: 24% with dyspnoea, 16% with reduced exercise tolerance and 60% with both symptoms. The mean age of the participants was 74.6 (SD ±6.3) years and 50% were male. Important co-morbidities were hypertension (70%), diabetes mellitus (31%), ischemic heart disease (31%), hypercholesterolemia (28%), osteo-arthritis (25%) and visual impairment (25%). The most frequently used drugs are related to these co-morbidities. All baseline characteristics of the included patients are described in Table 2.

**Table 2 T2:** Baseline characteristics

	**All**	**Diagnostic screening**	**Care as usual**
	(*n* = 841)	(*n* = 395)	(*n* = 446)
Mean age in years ± sd	74.6 ± 6.3	75.4 ± 6.2	73.8 ± 6.3
Male sex, *n* (%)	418 (49.7%)	176 (44.6%)	242 (54.3%)
*Complaints*			
MRC Dyspnoea score, median (IQR)	2 (2–3)	2 (2–3)	2 (2–3)
Reduced exercise tolerance questionnaire score, median (IQR)	2 (1–3)	2 (0–3)	2 (1–3)
*Cardiovascular co-morbidities*			
Ischemic heart disease, *n* (%)	259 (30.8%)	127 (32.2%)	132 (29.6%)
Heart failure, *n* (%)	42 (5.0%)	22 (5.6%)	20 (4.5%)
Valvular disorders, *n* (%)	59 (7.0%)	24 (6.1%)	35 (7.8%)
Cardiac rhythm disorders, *n* (%)	116 (13.8%)	55 (13.9%)	61 (13.7%)
Hypertension, *n* (%)	591 (70.3%)	292 (73.9%)	299 (67.0%)
Hypercholesterolemia, *n* (%)	234 (27.8%)	94 (23.8%)	140 (31.4%)
Diabetes Mellitus, *n* (%)	262 (31.2%)	130 (32.9%)	132 (29.6%)
CVA or TIA, *n* (%)	99 (11.8%)	44 (11.1%)	55 (12.3%)
*Non-cardiovascular co-morbidities*			
Visual impairment, *n* (%)	207 (24.6%)	98 (24.8%)	109 (24.4%)
Hearing impairment, *n* (%)	93 (11.1%)	43 (10.9%)	50 (11.2%)
COPD, *n* (%)	134 (15.9%)	68 (17.2%)	66 (14.8%)
Asthma, *n* (%)	78 (9.3%)	36 (9.1%)	42 (9.4%)
Mood disorders, *n* (%)	27 (3.2%)	11 (2.8%)	16 (3.6%)
Urinary tract problems, *n* (%)	90 (10.7%)	35 (8.9%)	55 (12.3%)
Osteoporosis, *n* (%)	58 (6.9%)	25 (6.3%)	33 (7.4%)
Malignancies, *n* (%)	51 (6.1%)	18 (4.6%)	33 (7.4%)
Anaemia, *n* (%)	14 (1.7%)	9 (2.3%)	5 (1.1%)
Renal insufficiency, *n* (%)	47 (5.6%)	12 (3.0%)	35 (7.8%)
Thyroid dysfunction, *n* (%)	63 (7.5%)	28 (7.1%)	35 (7.8%)
Osteoarthritis, *n* (%)	212 (25.2%)	126 (31.9%)	86 (19.3%)
Co-morbidities (number), median (IQR)	3 (3–4)	4 (3–4)	3 (3–5)
*Drugs*			
Diuretics, *n* (%)	346 (41.1%)	169 (42.8%)	177 (39.7%)
ACE-i/ARBs, *n* (%)	478 (56.8%)	220 (55.7%)	258 (57.8%)
ß-blockers, *n* (%)	397 (47.2%)	185 (46.8%)	212 (47.5%)
Digitalis, *n* (%)	20 (2.4%)	12 (3.0%)	8 (1.8%)
Oral anticoagulants, *n* (%)	117 (13.9%)	49 (12.4%)	68 (15.2%)
Platelet antagonists, *n* (%)	402 (47.8%)	192 (48.6%)	210 (47.1%)
Treatment for hypercholesterolemia	488 (58.0%)	209 (52.9%)	279 (62.6%)
Anti-diabetic drugs, *n* (%)	223 (26.5%)	109 (27.6)	114 (25.6%)
Treatment for COPD or Asthma, *n* (%)	204 (24.3%)	91 (23.0%)	113 (25.3%)
Drugs (number), median (IQR)	6 (4–7)	5 (4–7)	6 (4–7)

baseline characteristics at selection based on electronic medical fileI Ischemic heart disease includes prior myocardial infarction, angina pectoris, coronary artery bypass grafting, and percutaneous coronary intervention; visual impairment includes cataract, blindness or glaucoma, ACE-i = angiotensin converting enzyme-inhibitor, ARBs = angiotensin receptor blockers.

In total 395 participants were included in the diagnostic screening group and 446 in the care as usual group. The distribution of co-morbidities and drug use of the two arms are shown in Table 2.

## **Discussion**

The screening arm of the trial will generate data on the proportion of frail elderly with reduced exercise tolerance and/or exercise induced dyspnoea that have unrecognized HF, COPD and other chronic diseases (like anaemia, renal dysfunction, thyroid disorders). The comparison of the screened versus usual care arm within this clustered randomized trial will reveal whether screening and subsequent targeted interventions would be beneficial for frail elderly with respect to functional health and/or health related quality of life after 6 months of follow-up. The cost-effectiveness will also be examined.

## Abbreviations

HF, Heart failure; COPD, Chronic obstructive pulmonary disease; GP, General practitioner; MRC dyspnoea, Medical Research Counsel dyspnoea scale; MDS, Minimal data set; SF-36, Short form-36; ECG, Electrocardiogram; NT-pro-BNP, Amino-terminal pro-B-type natriuretic peptide; VAS, Visual analog scale; HFPEF, Heart failure with preserved ejection fraction; LVH, Left ventricular hypertrophy; AF, Atrial fibrillation; Hb, Haemoglobin; MDRD, Modification of diet in renal disease; EGFR, Estimated glomerular filtration rate; TSH, Thyroid-stimulating hormone; FT4, Free thyroxin 4; EQ-5D_index, Index EuroQol Five-Dimensional Questionnaire.
